#### 2.2.2. Exclusion Criteria

HCWs, TAs, SAs, and MIs who received the COVID-19 vaccines as part of phase III clinical trials.

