### Objectives

This project aims to actively monitor the side effects and effectiveness of COVID-19 vaccines worldwide. The primary objectives of the project include:(a)To estimate the prevalence of both local and systemic side effects following each of the COVID-19 vaccines among healthcare workers (HCWs), teachers and academics (TAs), senior adults ≥65 years old (SAs), and minors ≤18 years old (MIs);(b)To evaluate the potential demographic and medical risk factors for the frequency and intensity of side effects;(c)To evaluate the long-term safety of COVID-19 vaccines.

The secondary objectives include:(a)To evaluate the relative effectiveness and safety of COVID-19 vaccines in relation to one another;(b)To evaluate the impact of palliative medications used by the vaccinated individuals for short-term side effect resolution.

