#### 2.1.1. Phase A

A validated, self-administered questionnaire will be developed and delivered online to the target population groups (HCWs, TAs, SAs, and MIs). In certain circumstances, telephone interviews and paper questionnaires will be used instead of the online questionnaire in order to adapt to the local setting. The questionnaire will inquire about the short-term side effects following either the first dose, the second dose, or both doses of the COVID-19 vaccine. The side effects will be classified as local or systemic, and their onset, duration, and intensity will be self-assessed and self-reported by the participating subjects. This phase is planned to take place until 31 December 2021.

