#### 2.2.1. Inclusion Criteria

HCWs, TAs, SAs, and MIs who received a COVID-19 vaccine in the post-authorization phase;The recently vaccinated individuals who received their vaccine dose within the previous 30 days will be prioritized to be invited for the study, even though the study will not be limited to the recently vaccinated individuals;Participating subjects should be at least 18 years old in order to give their informed consent independently, or in case of the minors (below 18 years old), their caregivers will be asked to give their informed consent.

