### 2.3. Instrument

The questionnaire will be based on the growing evidence of COVID-19 vaccines’ side effects, and adverse reactions and will be updated and validated accordingly. The questionnaire consists of four categories: (a) demographic data (age, gender, height, weight, profession, and geographic region); (b) medical anamneses (chronic illnesses, medications, smoking, and alcohol consumption); (c) COVID-19-related anamneses (type of vaccine, number of vaccine doses, dates of vaccine doses, previous infection, and diagnosis date); and (d) vaccine side effects (local side effects, systemic side effects, onset, and duration) Table S1.

The multi-linguistic versions of the instrument will be produced through a pragmatic workflow for translation and cultural adaptation [31]. The current instrument is designed and validated for the HCWs group. The instrument will be validated for the other two populations of interest (OAs and TAs) by a validation process using a panel of experts, with four experts from the targeted population and four experts with a background in public health, epidemiology, infectious disease, and vaccination.

Two native speakers of the target language with a high level of English proficiency will translate the instrument independently. An expert panel composed of three members (the two forward translators, and a third native speaker with a biomedical background and an advanced grasp of the English language) will review the two translated versions, and will resolve discrepancies between them, aiming to generate a harmonized final version. The working version will undergo reliability testing through test–retest. In the test–retest, a minimum of 10 volunteers should fill in the questionnaire twice, at least two weeks apart.

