### 2.7. Analysis

Descriptive statistics will be performed to check the normality of data distribution, and to present the frequencies and percentages of dependent variables (side effects) and independent variables (demographic data, medical anamneses, and COVID-19-related anamneses). Inferential statistics will be performed to evaluate the potential association of each side effect and the suggested demographic and medical risk factors. All tests will be performed using SPSS 27 (IBM Corp, Armonk, NY, USA), and the significance level cutoff will be set at *p* ≤ 0.05 [32].

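### Symptoms of a COVID-19 infection close to a dose can be counted as systemic vaccine side effects, because nothing in the plan relates diagnosis date to dose date

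*Protocol article*

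**What the plan says.** Section 2.2.1 admits "HCWs, TAs, SAs, and MIs who received a COVID-19 vaccine in the post-authorization phase" and sets no condition on infection status. Section 2.2.2 has a single exclusion: "HCWs, TAs, SAs, and MIs who received the COVID-19 vaccines as part of phase III clinical trials".

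In section 2.1.1 side effects are classed as local or systemic, and "their onset, duration, and intensity will be self-assessed and self-reported by the participating subjects". Neither that section nor section 2.3 describes a step that separates a vaccine reaction from symptoms of an infection present at the same time.

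Section 2.3 lists the COVID-19 items in the questionnaire: "type of vaccine, number of vaccine doses, dates of vaccine doses, previous infection, and diagnosis date". Both dates needed to place an infection relative to a dose are therefore asked for, at least for infections before the dose.

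Section 2.7 tabulates "independent variables (demographic data, medical anamneses, and COVID-19-related anamneses" and then uses inferential statistics to "evaluate the potential association of each side effect and the suggested demographic and medical risk factors". The only subgroup analysis announced is by time from vaccination to survey (Strengths and Limitations). That section names recall bias and the varying time span as limitations, but not concurrent infection.

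**The concern.** Primary objective (a) is "To estimate the prevalence of both local and systemic side effects following each of the COVID-19 vaccines", and primary objective (b) concerns risk factors for these effects. Fever, fatigue, headache and muscle pain can come from the vaccine or from COVID-19. If someone infected around the dose reports them, the plan as written has no way to tell the two causes apart, and the symptom enters the numerator of a systemic side effect.

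The same gap affects objective (b). An infection months before vaccination is a candidate risk factor for reacting to the vaccine. An infection at the time of the dose is a rival cause of the symptom. Unless timing is used, one previous-infection variable can hold both.

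What is at stake is the accuracy of the estimates for individual systemic effects, which section 2.7 analyses one by one, and the meaning of the previous-infection association.

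**Working it through.** **1. The plan's own figure.** Section 2.2.3 and Figure 1 use an expected frequency of 60%, a 5-point margin and a design effect of 1.

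- n0 = z² × p(1 − p)/d² = z² × 0.24/0.0025, which is 368.8 at 95% and 637.0 at 99% confidence.
- The population size is in a figure not shown. With an assumed N of 200,000, N × n0/(n0 + N − 1) gives 368.1 and 634.9.

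This reproduces the stated 368–635. The sample size is sound on its own terms and is not affected by this point.

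**2. Inputs for the size of the effect.** The document gives none of these, so all are assumptions:

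- q, the share of respondents infected close to a dose: 0.5–2%, widened to 5% in step 4;
- s, the share of those who report a given symptom as a side effect: 60%, varied over 50–80% in step 4;
- p, the true prevalence of the symptom after vaccination: 3%, 10% or 30%.

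**3. Main calculation.** Observed = (1 − q) × p + q × s, with s = 60%.

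| True p | q = 0.5% | q = 2% | Relative inflation |
|---|---|---|---|
| 3% | 2.985 + 0.3 = 3.29% | 2.94 + 1.2 = 4.14% | 9.5–38% |
| 10% | 9.95 + 0.3 = 10.25% | 9.8 + 1.2 = 11.0% | 2.5–10% |
| 30% | 29.85 + 0.3 = 30.15% | 29.4 + 1.2 = 30.6% | 0.5–2% |

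**4. Second form, wider ranges.** If an infected respondent can have the symptom from either cause, independently, then observed = p + (1 − p) × q × s. With q from 0.5% to 5% and s from 50% to 80%:

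- p = 60%: +0.1 to +1.6 points;
- p = 10%: +0.2 to +3.6 points (ratio 1.02–1.36);
- p = 5%: +0.2 to +3.8 points (ratio 1.05–1.76).

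**5. Against sampling error.** At p = 3% and n = 368 the 95% half-width is 1.96 × √(0.03 × 0.97/368), about 1.7 points. The shift in step 3 is 0.3–1.1 points, so one national group sample would not show it. Under simple random sampling, the half-width equals the shift when n = 1.96² × 0.03 × 0.97/shift² = 0.1118/shift². That is about 860 respondents for 1.14 points (q = 2%) and about 13,800 for 0.285 points (q = 0.5%). The bias does not shrink with sample size, so it matters mainly once countries are pooled.

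**6. Direction for the previous-infection association.** If infections around the dose are recorded as previous infection, their symptoms push the association up. If the item records only infections before the dose, cases arising just after it fall in the uninfected group and push it down. The item's wording is in Table S1, which is not shown.

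**The case against.** The strongest objection is that this is analysis-plan detail. The remedy leaves the exclusion criteria alone and asks for a filter and a variable definition, which an analysis plan not shown may already contain; a journal article's one-paragraph analysis section need not. This carries weight, and silence alone would not be a finding. What stands is that the article does state who is eligible, how side effects are ascertained and what role COVID-19 history plays. Followed as written, those three statements let infection symptoms into the estimates.

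Second, the questionnaire asks about vaccine side effects, so a respondent who knows they had COVID-19 may not report its symptoms. That is fair. It lowers s and hence the bias, but does not make it zero.

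Third, simply dropping everyone diagnosed up to 14 days after a dose could discard genuine early reactions in people infected later. It would also select on testing that symptoms had prompted. This stands, and is why the fix uses symptom onset and reports both versions.

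A reader might also infer three stronger things that the document does not support:

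- **That previous infection is analysed as yes/no.** No section fixes its coding.
- **That the association with previous infection is biased upward.** Step 6 shows that it can go either way.
- **That differing infection levels will appear as differences between vaccines.** Section 2.2 describes the order of target groups in national roll-outs. The document gives neither brand allocation nor infection levels, so this is only a possibility.

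**Conclusion.** The point holds as a limited weakness: symptoms of an infection close to a dose can be counted as systemic vaccine side effects, and no stated step detects or separates them. No figure in the article is wrong.

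Neither size nor direction can be derived from the document. Under the assumed inputs the effect is negligible for overall prevalence near 60%, except at the extreme of the ranges tried, and modest for uncommon individual systemic effects. The larger relative figures, 38% at a true prevalence of 3% or a ratio of 1.76 at 5%, are upper ends of assumed ranges and should not be read as expected bias. All the calculations assume that infection symptoms are reported as side effects at rate s. The change is worth making because it is cheap and bears on primary objectives (a) and (b), chiefly in the pooled international results.

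**What to change.** - Keep eligibility as it is.
- Check that the diagnosis-date item also records infections diagnosed after a dose, and reword it if it does not.
- Prespecify a window around each dose; 14 days either side is an example, with no basis in the document. Report each systemic side effect with and without respondents whose diagnosis falls in it.
- In the restricted estimate, use reported symptom onset to keep reactions that clearly precede a later infection.
- Define the previous-infection risk factor as a diagnosis before that window.

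The cost is one extra analysis, possibly a small wording change to one item, and a slight loss of respondents in the restricted estimate. If 5% of 368 were removed, the margin of error at 60% would rise from 5.0 to about 5.1 points. Keeping 368 evaluable respondents would take 368/0.95, or 388.

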#### 2.2.3. Sample Size

The pragmatic sample size for each target group in each country will be calculated using Epi Info ^TM^ version 7.2.4 (CDC, Atlanta, GA, USA. 2020). The formula of population survey studies will be used to achieve a 5% margin of error and a 95–99% confidence level [29]. The expected frequency (outcome probability) is assumed to be 60%, as the prevalence of side effects following COVID-19 vaccines ranged between 62% and 93% in our previous studies [21,22] (Figure 1).

### 2.3. Instrument

The questionnaire will be based on the growing evidence of COVID-19 vaccines’ side effects, and adverse reactions and will be updated and validated accordingly. The questionnaire consists of four categories: (a) demographic data (age, gender, height, weight, profession, and geographic region); (b) medical anamneses (chronic illnesses, medications, smoking, and alcohol consumption); (c) COVID-19-related anamneses (type of vaccine, number of vaccine doses, dates of vaccine doses, previous infection, and diagnosis date); and (d) vaccine side effects (local side effects, systemic side effects, onset, and duration) Table S1.

The multi-linguistic versions of the instrument will be produced through a pragmatic workflow for translation and cultural adaptation [31]. The current instrument is designed and validated for the HCWs group. The instrument will be validated for the other two populations of interest (OAs and TAs) by a validation process using a panel of experts, with four experts from the targeted population and four experts with a background in public health, epidemiology, infectious disease, and vaccination.

Two native speakers of the target language with a high level of English proficiency will translate the instrument independently. An expert panel composed of three members (the two forward translators, and a third native speaker with a biomedical background and an advanced grasp of the English language) will review the two translated versions, and will resolve discrepancies between them, aiming to generate a harmonized final version. The working version will undergo reliability testing through test–retest. In the test–retest, a minimum of 10 volunteers should fill in the questionnaire twice, at least two weeks apart.

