### 2.2. Population

In Phase A, a pragmatic approach will be used, tracking each target population group according to individual governments’ distributional plans, which in most countries went from HCWs, to SAs, to TAs, to MIs. The sample of Phases B and C will be pre-identified based on the outcomes of Phase A.

If more than 368 of the Phase A participants show their interest in joining Phase B, no additional recruitment will be required. If less than 368 of the Phase A participants show their interest in participating in Phase B, additional recruitment will be carried out, targeting HCWs who will receive booster doses. In case of the emergence of special side effects after booster doses, additional recruitment of a sample of HCWs will be required.

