### 2.5. Timeline

As the local timelines are dependent on the setting of each participating country—including governments’ distribution plans, availability of vaccines, and administrative processes—the proposed timeline is deemed to guide the overall CoVaST progress (Table 1).

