### Strengths and Limitations

To the best of the authors’ knowledge, this is the first multinational study aiming to monitor the safety of various COVID-19 vaccines, especially following booster doses. Another strong point of this study is its unified evaluation instrument, target groups, and methods, which will be used in all participating countries, and should maximize the results’ internal validity. Recruiting HCWs is intended to limit the reporting bias that is naturally predicted in this survey-based study, due to the fact that HCWs retain high levels of health literacy and scientific interest. This study is one of the early-registered studies that are concerned with the long-term safety of COVID-19 vaccines, and their effectiveness.

In general, this study is limited by the heterogeneous time span between vaccination and survey commencement across the participating countries; therefore, subgroup analysis according to the time span will be carried out during data analysis. One more limitation is recall bias, as in various countries, vaccination covered the majority of population who intended to be vaccinated. Due to the recruitment of participants who received the vaccine in the first half of 2021, there is a possibility of recall bias when filling out the questionnaire. Since COVID vaccination is a hot topic worldwide, we assume that participants could remember all experienced side effects well.

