## Figures and Tables

**Figure 1 ijerph-18-07859-f001:**
[figure not shown]
Sample size of healthcare workers (HCWs) in the Czech Republic—Epi-Info ^TM^ version 7.2.4. Population size: Total number of healthcare workers in the Czech Republic in 2017 [30]. Expected frequency: The overall prevalence of side effects following COVID-19 vaccines ranged between 62% and 93%; therefore, 60% was assumed as a threshold. Acceptable margin of error: The permissible level for all CoVaST groups will be 5%. Design effect: One—per the recommendation of the CDC for simple sampling [29]. Clusters: One—per the recommendation of the CDC for simple sampling [29]. The pragmatic sample size is 368–635 (CI 95%–99%).

**Table 1 ijerph-18-07859-t001:** The projected timeline of the COVID-19 vaccines safety tracking (CoVaST) study.

Phase	Stage	Population	Schedule
Phase A	Stage A.1.	HCWs	May–August 2021
	Stage A.2.	SAs	June–December 2021
	Stage A.3.	TAs	June–December 2021
	Stage A.4.	MIs	June–December 2021
Phase B	Stage B.1.	HCWs	October 2021–February 2021
	Stage B.2.	SAs	November 2021–April 2022
	Stage B.3.	TAs	November 2021–April 2022
	Stage B.4.	MIs	November 2021–April 2022
Stage C	Stage C.1.	HCWs, SAs, TAs, MIs	January–December 2022
	Stage C.2.	HCWs, SAs, TAs, MIs	January–December 2023
	Stage C.3.	HCWs, SAs, TAs, MIs	January–December 2024
	Stage C.4.	HCWs, SAs, TAs, MIs	January–December 2025
	Stage C.5.	HCWs, SAs, TAs, MIs	January–December 2026

HCWs = Healthcare Workers; SAs = Senior Adults; TAs = Teachers and Academics; MIs = Minors.

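### The questionnaire may be updated while data are collected, with no fixed core list, so the unified-instrument claim is not secured and composite side-effect rates may depend on questionnaire version

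*Protocol article*

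**What the plan says.** Section 2.3 (Instrument) rests the questionnaire on accumulating evidence about side effects "and adverse reactions and will be updated and validated accordingly". It gives no date after which the list is closed and no set of items that stays constant. It adds that the present version was designed and validated for healthcare workers, with validation for other groups still to come.

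Sections 2.1.1 to 2.1.3 each say that a questionnaire will be developed for the phase concerned.

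Collection is spread over time. Section 2.2 follows the governments' roll-out order, "which in most countries went from HCWs, to SAs, to TAs, to MIs". Table 1 places healthcare workers in "May–August 2021" and seniors, teachers and minors all in "June–December 2021". Section 2.5 lets countries differ: "As the local timelines are dependent on the setting of each participating country".

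Strengths and Limitations then counts as a strength "its unified evaluation instrument, target groups, and methods, which will be used in all participating countries", and expects this to serve internal validity.

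Primary objective (a) is "To estimate the prevalence of both local and systemic side effects following each of the COVID-19 vaccines" in the four target groups. Secondary objective (a) sets the vaccines against one another on effectiveness and safety.

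**The concern.** A composite such as any side effect can only stay level or rise when items are added to the list. If the list changes during collection, two respondents with identical experience can be classified differently because they saw different versions. A prevalence pooled over versions then has no single definition, which touches primary objective (a).

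Version would follow calendar time. Calendar time is linked to target group through the roll-out order and Table 1, to country through the local timelines, and possibly to vaccine through availability. The comparison most exposed is the safety part of secondary objective (a): a difference between two vaccines could partly reflect which version their recipients answered. A change between Phases A and B would affect any reading of booster rates against first-course rates in the same way.

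The planned subgroup analysis by time between vaccination and survey does not deal with this, because that interval is not the questionnaire version. If version is not stored with the response, it may be impossible to recover reliably.

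**Working it through.** **1. The plan's own figure.** Inputs from Section 2.2.3: expected frequency p = 0.60, margin d = 0.05, confidence 95% and 99%. Formula: n0 = z² p(1−p)/d².

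- 95%: 1.96² × 0.24 / 0.0025 = 368.8
- 99%: 2.576² × 0.24 / 0.0025 = 637.0

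The finite-population correction is n0 / (1 + (n0 − 1)/N). N stands in a figure that is not shown. Assuming N between 200,000 and 300,000, the results are 368.1 to 368.3 and 634.9 to 635.6, which match the stated 368 and 635. The sample size is not in dispute. It supplies the yardstick: a rate near 60% and a 5-point margin.

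**2. The text side by side.** Section 2.3 allows the list to change as evidence grows. Table 1 and Section 2.5 spread Phase A over May to December 2021, with country differences. Nothing confines updates to the gaps between phases, and nothing keeps a common set of items across versions. The unified-instrument claim therefore depends on a condition that the text does not state.

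**3. Possible shift in a composite.** Let p be the rate with the shorter list, k the number of added items, and q the share of otherwise event-free respondents who report each added item. The items are taken as independent of one another. The new rate is 1 − (1 − p)(1 − q)^k, so the shift is (1 − p)[1 − (1 − q)^k]. Both k and q are assumptions. The base of 60% is the planning value, 93% is the top of the protocol's 62–93% range, and 80% is an intermediate value.

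| Added items | Shift at 60% | Shift at 80% | Shift at 93% |
|---|---|---|---|
| 1 at 1% | 0.40 | 0.20 | 0.07 |
| 5 at 1% | 1.96 | 0.98 | 0.34 |
| 5 at 3% | 5.65 | 2.83 | 0.99 |
| 5 at 5% | 9.05 | 4.52 | 1.58 |

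(Shifts in percentage points.) Worked case: 1 − 0.4 × 0.97⁵ = 0.6565 and 1 − 0.07 × 0.97⁵ = 0.9399.

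To move the composite by 5 points, the added items together must catch 0.05/(1 − p) of the non-reporters: 12.5% at a 60% base, 25% at 80% and 71% at 93%.

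**4. What a shift would do to a test.** Take two groups with the same true rate of 60%, one wholly on the shorter list and the other wholly on the longer, tested two-sided at 0.05 (the protocol gives 0.05; two-sided is assumed). The chance that the artefact alone tests significant, in its own direction, is:

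| Shift | 368 per group | 635 per group |
|---|---|---|
| 2 points | 8% | 11% |
| 5 points | 29% | 45% |
| 9 points | 72% | 92% |

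Complete separation of versions is the extreme case. If shares f and g of the two groups receive the longer list, the gap is only (f − g) times the shift.

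**5. Single items.** An item present in the same form in every version is not shifted. For an item added when half the sample is complete, a true 10% would appear as 0.10 × 0.5 = 5% if everyone formed the denominator, and as 10% if only those asked did. The protocol does not say which denominator applies.

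**The case against.** The strongest reply is that the harmful sequence is not in the text. Section 2.3 gives neither timing nor direction: an update could reword or remove items, and the phase-by-phase wording of Sections 2.1.1 to 2.1.3 fits updating between phases. A common instrument revised centrally could still be called unified across countries. Section 2.7 tests each side effect separately, so most inference may not use a composite. Primary objective (a) estimates rates and does not contrast groups, and no objective compares countries or Phase B with Phase A. The illustration uses the 60% base, below the protocol's own 62–93% range, and co-occurring side effects would shrink the shift. Adding new effects is also a reasonable choice in active surveillance, and version fields and denominators are details that a condensed article may leave out.

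Much of this stands. A reader might infer that later groups are certainly asked about more events, or that late vaccines face a longer list. The documents do not support either: no text says that items will be added for a given group or vaccine, and the item list (Table S1) is not shown. A reader might also see the groups as surveyed one after another. Table 1 puts three of them in one window, which overlaps the healthcare workers' window from June to August. Nor may one conclude that the prevalences as a whole are not comparable.

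What does not stand is that this is only missing detail. The article itself states an updating rule driven by new evidence and, elsewhere, rests validity on one instrument. The first leaves the second unsecured whatever the full protocol adds on data handling.

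**Conclusion.** The concern holds in a conditional form. The stated updating rule, without a fixed core list and alongside staggered collection, allows added or changed items and the any, any-local and any-systemic composites to depend on questionnaire version. Version may in turn be associated with group, country or vaccine. The main exposure is the overall prevalence under primary objective (a) and the vaccine-to-vaccine safety comparison under secondary objective (a).

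The size cannot be determined from the documents. Under the assumptions shown it runs from negligible (0.4 points or less for one rare item) to more than the 5-point margin (five items at 3% or more from a 60% base), and it is small where the base rate is already high. It requires that updates fall within Phase A or between Phases A and B, and that versions are unevenly spread over what is compared. This is a cheap design improvement. It is not a demonstrated bias.

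**What to change.** In Section 2.3, fix a core list of local and systemic side effects before collection opens and use it unchanged in all groups, countries and phases. Put newly recognised effects in a supplementary module that may be updated, and store the questionnaire version with each response.

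In Section 2.7, define the composites and make all comparisons between groups, vaccines and phases on the core list only. For supplementary items, take as denominator only the respondents who were asked.

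The unified-instrument statement under Strengths and Limitations can then stand for the core list.

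The cost is one version field and a few sentences. The downside is that newly recognised effects do not count in the headline prevalence and are reported separately, on smaller numbers.
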